## **Lists of abbreviation**

OCT: optical coherence tomography

SD: spectral domain

CXL: corneal collagen crosslinking

## **Study Population:**

SD-OCT corneal scans of 20 eyes with keratoconus (group one) and 20 healthy eyes with > 2 diopters (D) of corneal astigmatism as controls (group two) will be studied. Keratoconus patients referred to the Eye Dpt. of the University Hospital North Norway for CXL-treatment and healthy subjects seeking preoperative evaluation for refractive surgery at SynsLaser Kirurgi AS Tromsø will be examined med corneal SD-OCT as a part of their routine examination. Analysis of their SD-OCT corneal scans will be used for the purpose of this study.

## **Study Design:**

Cross-sectional, non-interventional, observational study

## **Sample Size:**

Total number of participants: 40

## **Study Duration:**

May 1 to October 31, 2013

## **Primary Objective:**

To characterize epithelial and stromal thickness distribution in keratoconic eyes

## **Secondary Objectives:**

To develop epithelial and stromal thickness-based variables for keratoconus detection

## **Background and Significance:**

Corneal epithelium is a moldable and active corneal layer that keeps the optical quality of the eye by remodeling itself to compensate for any change in the stromal surface shape e.g. after keratorefractive surgery or in keratoconus. Mapping of the corneal epithelial thickness may help detect stromal surface irregularities like subclinical cones, before they become detectable on topography.

Mapping of the corneal epithelium has been previously attempted by use of various technologies such as ultrasound, confocal microscopy and Optical coherence tomography (OCT).

OCT has been developed for non-contact, cross-sectional imaging in biological systems by using low-coherence interferometry to produce a two-dimensional image of optical scattering from internal tissue microstructures in a way that is analogous to ultrasonic pulse-echo imaging. Spectral domain (SD), a newer generation OCT to be used in the current study, seems to be reliable and reproducible in measuring corneal epithelial thickness in contrast to the measurements with the time domain OCT and does not require immersion like very-high-frequency digital-ultrasound, which is the only method providing sufficient resolution for corneal epithelial imaging.

A recently published study utilizing the SD-OCT technology compares the epithelial thickness distribution of keratoconic corneas with the corneas of healthy subjects with unspecified amount of astigmatism, while the current study will use healthy corneas with > 2D of astigmatism as the control group.

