## **Methodology:**

SD-OCT scans of 20 eyes with keratoconus (group one) and twenty healthy eyes with > 2 diopters (D) of corneal astigmatism as controls (group two) will be analyzed. Two cross-sectional meridional corneal profiles (along steepest and flattest meridians, located by a Scheimpflug-based corneal topography) for each individual will be obtained by using a RTVue100 (Optovue Inc. Fremont, California, USA), 26000-Hz SD-OCT across the central 6mm diameter of the cornea.

To map the epithelial and stromal thickness distribution in eyes from group one, 11 locations will be measured: corneal vertex, cone apex, mid-peripheral cornea (1.5mm from corneal vertex) and peripheral cornea (2.5mm from corneal vertex) along both the steepest and flattest meridian, and the locations with thickest epithelium along the steepest meridian. In eyes from group two, 11 corresponding locations will be measured.

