## **Inclusion /Exclusion Criteria**

SD-OCT scans of 20 confirmed cases of keratoconus referred to CXL treatment at the University Hospital North Norway and 20 healthy subjects seeking refractive surgery at SynsLaser Kirurgi AS in Tromsø for astigmatism >2 D will be used. The participants will be the subjects to the inclusion/exclusion criteria by the two institutions, regarding keratoconus and candidacy for refractive surgery, respectively.

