## **Statistical Analysis Plan:**

Statistical analysis will be performed using SPSS 13.0 software. The independent-samples t test will be used to assess the difference of epithelial and stromal thickness at corresponding locations between two groups and between different locations within group.

Descriptive statistics will be carried out for all eyes using vertical mirrored symmetry superimposition: thickness values for left eyes will be reflected in the vertical axis and superimposed onto the right eye values so that nasal/temporal characteristics could be combined.

The sample size was decided by the power calculation founded on data from the previous studies analyzing corneal epithelial thickness in keratoconus and healthy eyes. For a significance level of 0.05 and a statistical power of 0.8, the equation for sample size is:  $N=31.4 \times \sigma^2 / D^2$ , where  $\sigma$  is assumed standard distribution of each group and D is the minimum expected difference between two means. According to the preliminary data collected from comparable studies, population  $\sigma$  and D are chosen to be 5.0 and 4.7 respectively, yielding a sample size  $N=35.5$ . In the current study we chose a sample size 40.

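### The group comparison is an unadjusted t test between two differently recruited groups with no age rule or matching stated; an age-adjusted model should stand beside it

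*Protocol*

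**What the plan says.** - **Controls.** The Methodology section states that "twenty healthy eyes with > 2 diopters (D) of corneal astigmatism as controls (group two) will be analyzed". The Inclusion/Exclusion Criteria section gives their source: "20 healthy subjects seeking refractive surgery at SynsLaser Kirurgi AS in Tromsø for astigmatism >2 D will be used".
- **Cases.** The same section defines group one as "20 confirmed cases of keratoconus referred to CXL treatment at the University Hospital North Norway". It sets no astigmatism floor, ceiling or range for them.
- **All other eligibility.** This is left to each clinic: "The participants will be the subjects to the inclusion/exclusion criteria by the two institutions, regarding keratoconus and candidacy for refractive surgery, respectively". Those criteria are not reproduced. The protocol mentions neither age, sex nor matching.
- **Reason given for the control group.** Background and Significance contrasts this study with an earlier one whose controls had an unspecified amount of astigmatism, and then says that "the current study will use healthy corneas with > 2D of astigmatism as the control group".
- **Analysis.** The Statistical Analysis Plan section states: "The independent-samples t test will be used to assess the difference of epithelial and stromal thickness at corresponding locations between two groups". It names no covariate, stratum or adjusted model.

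**The concern.** The comparison is not randomised. The two groups come from different clinics, for different reasons, under different eligibility rules. An unadjusted t test estimates the total difference between them, which includes anything that comes from age or astigmatism as well as from keratoconus. A floor on astigmatism in one group, with no criterion in the other, does not make the groups alike on it: controls could be more or less astigmatic than cases.

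Both objectives are touched. Describing thickness in keratoconic eyes against controls relies on the contrast reflecting the disease. Detection variables built from groups that also differ in age could partly be separating ages. The protocol itself describes the epithelium as remodelling in response to changes in stromal surface shape, so features of corneal shape other than keratoconus may plausibly affect the outcome.

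The protocol carries its own analysis section and names the test there, and the choice of controls is a design matter. The point is therefore about what this document fixes, not about detail left to a separate plan.

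**Working it through.** **Inputs from the protocol** (Statistical Analysis Plan and Study Population sections): alpha 0.05, power 0.80, σ = 5.0, D = 4.7, 20 eyes per group. Units for σ and D are not given.

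**Step 1: the protocol's own figure.** N = 31.4 × σ²/D² = 31.4 × 25/22.09 = 35.5, as stated. The constant is 4 × (1.960 + 0.842)² = 31.4, so N is the total for a two-sided, 1:1, unadjusted comparison of two means. With 20 per group the standard error is 5 × √(2/20) = 1.581 and the noncentrality is 4.7/1.581 = 2.973. On 38 degrees of freedom the power is 0.83. The sample size is sound for the test as written, and this point does not rest on a sample-size error.

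**Step 2: what an uncontrolled offset would do.** The protocol gives no age or astigmatism distributions and no slopes of thickness on either, so the offset b is assumed. For instance, 10 years × 0.1 per year, or 2 D × 0.5 per dioptre, gives b = 1. The rejection rate comes from the noncentral t with noncentrality b/1.581 when there is no true difference, and (4.7 − b)/1.581 when b opposes a true difference of 4.7.

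| Assumed offset b | b/4.7 | Rejection, no true difference | Power at 4.7, b opposing |
|---|---|---|---|
| 0 | 0% | 5% | 0.83 |
| 0.5 | 11% | 6% | 0.74 |
| 1 | 21% | 9% | 0.63 |
| 2 | 43% | 23% | 0.38 |

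These are rates for one location. The range starts at zero because nothing in the protocol rules zero out.

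**Step 3: what adjustment would cost.** Let R²g be the share of the variance in group membership that age explains, and R²y the share of within-group thickness variance that it explains. The noncentrality becomes 2.973 × √[(1 − R²g)/(1 − R²y)], on 37 degrees of freedom with one covariate. With R²g = 0.20 and R²y = 0 it is 2.973 × √0.8 = 2.659.

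| Assumed R²g | Power, R²y = 0 | Power, R²y = 0.20 |
|---|---|---|
| 0 | 0.83 | 0.90 |
| 0.20 | 0.74 | 0.83 |
| 0.30 | 0.68 | 0.77 |
| 0.50 | 0.53 | 0.63 |

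With equal groups, R²g = d²/(d² + 4), where d is the age difference in within-group SDs. R²g = 0.20 therefore means groups one SD apart in age (1/5 = 0.20). When R²g equals R²y, the loss and the gain cancel.

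**The case against.** The best defence is that the design suits the stated aims. Those aims are descriptive (characterise thickness in keratoconic eyes) and diagnostic (derive detection variables), and neither strictly needs an adjusted effect. Astigmatic controls are a more demanding comparator than unselected normal eyes and resemble the candidates whom screening would meet. Astigmatism is partly a consequence of keratoconus, so leaving cases unrestricted and not adjusting for it is defensible. A matching floor on cases would narrow the very spectrum to be described. Most of this stands, and it is why the change proposed here concerns age first.

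A reader might infer that the protocol claims to separate keratoconus from astigmatism and fails at it. The text does not support that. Background and Significance only specifies the comparator and contrasts it with that of an earlier study. It claims neither equal astigmatism nor that every difference is due to keratoconus.

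A reader might also conclude that the groups are matched on nothing. The supportable statement is that no matching is stated: the clinics' own criteria are not shown and may limit age.

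Finally, the offsets in the working are assumptions, and the false-positive rates apply only where there is no true difference, whereas the study is planned for D = 4.7. That is correct, and it limits the tables to illustrating scale.

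**Conclusion.** The point holds as a risk of bias that the stated analysis leaves open. The facts behind it are in the text: an astigmatism rule for one group only, two recruitment streams with separate eligibility rules, no age criterion or matching stated, and an unadjusted test. The restriction on controls deals with part of the astigmatism question and none of the age question.

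The size is unknown. Over assumed offsets of 0 to 2 units, the per-location false-positive rate runs from 5% to 23%, and power against an opposing offset runs from 0.83 down to 0.38. This assumes σ = 5.0 as planned, and the direction could be either way. It does not show that the comparison is biased. It does show that a modest addition to the analysis would let the reader judge.

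**What to change.** In the Statistical Analysis Plan section:

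1. Keep the between-group t test as stated.
2. Beside it, add for each location a linear model of thickness on group adjusted for age. Report the adjusted difference with its 95% confidence interval.
3. Tabulate age, sex and corneal astigmatism by group.
4. Optionally, add a model that also adjusts for corneal astigmatism, using the Scheimpflug topography already used to locate the meridians. Label it exploratory, because astigmatism is partly a consequence of keratoconus and adjusting for it may remove some of the disease effect.

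Do not restrict cases to more than 2 D: that would shrink group one by an unknown amount and narrow the range of disease described.

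**Cost.** A few lines of text and no added examination, provided that age and sex are in both clinics' records, which the protocol does not state but which is likely. The statistical price is one degree of freedom plus lost precision if age differs strongly between the groups: power of about 0.74 instead of 0.83 in the 20% example, and about 0.53 if age explained half of group membership and none of the thickness variance. That is why the adjusted model should accompany the t test and not replace it.

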## **Purpose of the study:**

To characterize epithelial and stromal thickness distribution in keratoconic eyes and to develop epithelial and stromal thickness-based variables for keratoconus detection.

## **Methodology:**

SD-OCT scans of 20 eyes with keratoconus (group one) and twenty healthy eyes with > 2 diopters (D) of corneal astigmatism as controls (group two) will be analyzed. Two cross-sectional meridional corneal profiles (along steepest and flattest meridians, located by a Scheimpflug-based corneal topography) for each individual will be obtained by using a RTVue100 (Optovue Inc. Fremont, California, USA), 26000-Hz SD-OCT across the central 6mm diameter of the cornea.

To map the epithelial and stromal thickness distribution in eyes from group one, 11 locations will be measured: corneal vertex, cone apex, mid-peripheral cornea (1.5mm from corneal vertex) and peripheral cornea (2.5mm from corneal vertex) along both the steepest and flattest meridian, and the locations with thickest epithelium along the steepest meridian. In eyes from group two, 11 corresponding locations will be measured.

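### The eleventh location is chosen because its epithelium is thickest, so within-group epithelial tests against other locations are biased upward and their p-values cannot be interpreted

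*Protocol*

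**What the plan says.** Under Methodology, the list for keratoconic eyes opens: "11 locations will be measured: corneal vertex, cone apex, mid-peripheral cornea (1.5mm from corneal vertex) and peripheral cornea (2.5mm from corneal vertex". The mid-peripheral and peripheral points are taken on each of the two meridians, and the list ends with "and the locations with thickest epithelium along the steepest meridian". The count is one vertex, one cone apex, four mid-peripheral and four peripheral points, which makes ten, plus the thickest-epithelium point as the eleventh. For controls the section says only: "In eyes from group two, 11 corresponding locations will be measured".

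Under Statistical Analysis Plan, the between-group part reads: "The independent-samples t test will be used to assess the difference of epithelial and stromal thickness at corresponding locations between two groups". The same test is then extended to comparisons "between different locations within group". No location is excepted. Nothing says that the thickest-epithelium point is descriptive only, or that it is found on one scan and measured on another.

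**The concern.** Ten of the locations are defined by distance from the vertex or by the cone. The eleventh is defined by the outcome itself. If its epithelium is tested against the vertex or a peripheral point of the same meridian, the direction of the answer is known before any eye is scanned. What remains is the amount by which a maximum exceeds an unselected value, and that amount is positive even if the true mean thickness is the same everywhere.

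The control group raises a second question. *Corresponding* could mean each control eye's own thickest point, or the position in the control eye that matches where the maximum lay in keratoconus. Under the second reading a selected maximum is set against an unselected value.

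This matters because the primary objective is to describe the thickness distribution and the secondary objective is to build detection variables from it. Part of any thickening reported at this point would be a product of the selection, and the planned test cannot separate that part from a real one.

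**Working it through.** **The plan's own figure.** 31.4 × 5.0² / 4.7² = 31.4 × 25 / 22.09 = 35.5, as stated. The constant is 4 × (1.960 + 0.842)² = 31.4, that is, two-sided 0.05 and power 0.80 for the total of two equal groups. The sample size reproduces and is not at issue; it supplies the scale.

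**Inputs from the protocol.** 20 eyes per group; SD 5.0; planned difference 4.7; significance level 0.05; independent-samples t test. The protocol prints no unit for 5.0 and 4.7; micrometres are assumed.

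**Inputs that are assumptions.** Equal true mean thickness at every point; within-eye correlation ρ between points, from 0 to 0.95; five candidate points, with an effect common to the eye and independent residuals. The protocol gives none of these.

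**Built-in excess.** The expected maximum of five independent standard normal values is 1.163. The effect common to the eye cancels in the difference, so the mean excess of the maximum over the vertex is 1.163 × 5.0 × √(1 − ρ).

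**Rejection rates.** These were simulated with no true difference anywhere, 20 eyes per group.

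| ρ | Mean excess over vertex | Share of 4.7 | Planned independent t test | Paired t test |
|---|---|---|---|---|
| 0 | 5.8 | 124% | about 100% | 100% |
| 0.5 | 4.1 | 87% | 91% | 100% |
| 0.8 | 2.6 | 55% | 25% | 100% |
| 0.95 | 1.3 | 28% | about 0% | 100% |

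For comparison, a location fixed in advance (2.5 mm against the vertex) is rejected by the independent test in at most about 6% of studies.

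**Why the independent test falls away.** With 20 values on each side and SD near 5, it needs a difference of about 2.02 × 5 × √(2/20) = 3.2. As ρ rises, the built-in excess drops below that threshold and also varies less from study to study, so it is still present but seldom declared significant.

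**Sensitivity to the candidate points, at ρ = 0.8.** With 13 independent points the independent test rejects in 83% of studies. With a smooth profile of 61 points it rejects in 29% (correlation length 1 mm) or 2% (2 mm). The paired test rejects in 100% throughout.

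**Other meridian.** Against a flattest-meridian point the ordering is no longer guaranteed, but the bias remains: with five candidate points the independent test rejects in about 98%, 86%, 27% and 0% at the four correlations.

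**Between groups, five points.** If every eye contributes its own maximum, false rejection is about 5%. If keratoconus maxima are compared with a fixed control position, it runs from 99% at ρ = 0 through 78% and 38% to 13% at ρ = 0.95.

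**The case against.** A reader might infer that the comparison is significant by construction, whatever the truth. The documents do not support that. The protocol names the independent-samples test, and under that test the rejection rate runs from about 100% to 0% over the correlations considered. Certain rejection belongs to a paired test, which is not planned.

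The scope can also be overread. The strict ordering holds only for epithelium on the steepest meridian. Flattest-meridian points, and a cone apex lying off the steepest meridian, may be thicker in a given eye. Stromal thickness is not the selection variable.

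Nor does the protocol establish a spurious difference between the groups. If *corresponding* means the same definition applied to each control eye, that comparison is sound. The text is open on this and needs a clarifying phrase.

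The figures rest on assumed inputs, and the five-point model is a simplification. The vertex and the four fixed points already make five on the steepest meridian, so a separate eleventh location suggests a search along the whole scan, where neighbouring values are correlated. The sensitivity results show that this can move the rejection rate either way.

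Finally, locating the thickest epithelium is a legitimate part of mapping, and only one of eleven locations is affected.

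All of this stands, and it limits the size of the claim. It does not remove the defect: the location is chosen on the outcome, the stated within-group tests include it, and neither the sign nor the upward bias on the steepest meridian depends on the correlation or on the exact number of points searched.

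**Conclusion.** The plan is wrong as written on this point. Within group, an epithelial comparison of the thickest-epithelium location with any other point searched on the steepest meridian has its sign fixed in advance and its size biased upward. Compared with points off that meridian it is biased upward only. In neither case can the p-value be interpreted.

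Under the stated assumptions (flat profile, SD 5.0, five candidate points) the bias is 1.3 to 5.8, or 28% to 124% of the planned difference. How often it reaches significance under the named test cannot be determined from the protocol, because it depends on a within-eye correlation and a search rule that are not given. A non-significant result would be no more informative than a significant one.

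The between-group comparison is valid at about 5% if both groups follow the same rule. It is inflated to between 13% and 99% over the same correlations if they do not. The sample size is unaffected. The change should be made, since the defect lies in a stated rule and is easily removed.

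**What to change.** - In the Statistical Analysis Plan section, leave the thickest-epithelium location out of the within-group epithelial location tests. Within each group, report its thickness and its distance and direction from the vertex descriptively.
- In Methodology, state that the point is found by the same search rule, over the same length of the steepest-meridian scan, in every keratoconus and control eye. Compare it between groups only under the name *maximum epithelial thickness along the steepest meridian*.
- Stromal thickness at that point may still be compared between groups under the same rule.

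The cost is two or three sentences. No new measurements are needed, because the protocol already obtains the same central 6 mm profile along the steepest meridian for every participant.

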## **Inclusion /Exclusion Criteria**

SD-OCT scans of 20 confirmed cases of keratoconus referred to CXL treatment at the University Hospital North Norway and 20 healthy subjects seeking refractive surgery at SynsLaser Kirurgi AS in Tromsø for astigmatism >2 D will be used. The participants will be the subjects to the inclusion/exclusion criteria by the two institutions, regarding keratoconus and candidacy for refractive surgery, respectively.

## **Study Schedule:**

SD-OCT scans obtained from May 1, 2013 through August 31, 2013 will be analyzed.

## **Statistical Analysis Plan:**

Statistical analysis will be performed using SPSS 13.0 software. The independent-samples t test will be used to assess the difference of epithelial and stromal thickness at corresponding locations between two groups and between different locations within group.

Descriptive statistics will be carried out for all eyes using vertical mirrored symmetry superimposition: thickness values for left eyes will be reflected in the vertical axis and superimposed onto the right eye values so that nasal/temporal characteristics could be combined.

The sample size was decided by the power calculation founded on data from the previous studies analyzing corneal epithelial thickness in keratoconus and healthy eyes. For a significance level of 0.05 and a statistical power of 0.8, the equation for sample size is:  $N=31.4 \times \sigma^2 / D^2$ , where  $\sigma$  is assumed standard distribution of each group and D is the minimum expected difference between two means. According to the preliminary data collected from comparable studies, population  $\sigma$  and D are chosen to be 5.0 and 4.7 respectively, yielding a sample size  $N=35.5$ . In the current study we chose a sample size 40.

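### Comparisons between locations in the same eyes are assigned an independent-samples t test, although the measurements are paired

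*Protocol*

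**What the plan says.** The Statistical Analysis Plan section of the protocol assigns a single inferential test: "The independent-samples t test will be used to assess the difference of epithelial and stromal thickness at corresponding locations", and the same sentence gives its scope as "between two groups and between different locations within group". One verb governs both uses. The protocol names no paired t test, repeated-measures analysis or mixed model.

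The Methodology section fixes the data structure. For the keratoconic eyes, "To map the epithelial and stromal thickness distribution in eyes from group one, 11 locations will be measured"; for the controls, "In eyes from group two, 11 corresponding locations will be measured". There are 20 eyes in each group ("SD-OCT scans of 20 eyes with keratoconus (group one) and twenty healthy eyes"), and the Sample Size section states "Total number of participants: 40", which means one eye per participant.

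**The concern.** An independent-samples t test requires the two sets of readings to be independent. That holds for keratoconic against healthy eyes, which belong to different people. It does not hold for two locations within a group, say the vertex and a peripheral point, because both come from the same 20 corneas. An eye with a thick cornea at one point will tend to be thick at another, and the test treats this shared variation as noise in the difference.

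The Primary Objective is to describe how epithelial and stromal thickness are distributed in keratoconic eyes. Differences between locations bear directly on that. With the wrong test their p-values and confidence intervals are not valid, and real regional differences may go undetected.

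This is not a detail left to a separate analysis plan. The protocol states the test, and a later plan would have to contradict that sentence to be right.

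**Working it through.** **Inputs from the protocol:** n = 20 eyes per group and 11 locations per eye (Methodology); σ = 5.0 and D = 4.7, units not stated, significance level 0.05 and power 0.8 (Statistical Analysis Plan).

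**Assumptions, not in the protocol:** within-eye correlation ρ between two locations, shown from −0.5 to 0.9; a true regional difference of 2 units; the same SD of 5.0 at both locations.

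**The plan's own figure first.** The constant is 4(z₀.₉₇₅ + z₀.₈₀)² = 31.40, and N = 31.4 × 5.0² / 4.7² = 785 / 22.09 = 35.5. The stated figure reproduces as a two-sided, 1:1 total. With 20 per group the power is 84% by the normal approximation and 82.6% by the t test. This calculation concerns the two groups and contains no within-eye contrast.

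**Standard error of a difference between two locations in one group.**

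- Independent test: σ√(2/n) = 5.0 × √(2/20) = 1.581, with 2 × 20 − 2 = 38 degrees of freedom.
- Paired test: σ√(2(1−ρ)/n), with 20 − 1 = 19 degrees of freedom.
- Ratio, independent to paired: 1/√(1−ρ). For example, at ρ = 0.7 it is 1/√0.3 = 1.83.

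**Type I error and power**, from 200,000 simulated data sets of 20 correlated pairs per setting, nominal two-sided 5%:

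| ρ | Paired SE | SE ratio | Type I error, independent | Power for 2 units, independent | Power for 2 units, paired |
|---|---|---|---|---|---|
| −0.5 | 1.936 | 0.82 | 10.9% | 28.2% | 16.6% |
| −0.3 | 1.803 | 0.88 | 8.4% | 26.3% | 18.3% |
| 0 | 1.581 | 1.00 | 5.0% | 23.5% | 22.5% |
| 0.3 | 1.323 | 1.20 | 2.1% | 19.4% | 29.8% |
| 0.5 | 1.118 | 1.41 | 0.7% | 16.2% | 39.5% |
| 0.7 | 0.866 | 1.83 | 0.1% | 11.5% | 59.1% |
| 0.8 | 0.707 | 2.24 | 0.01% | 8.4% | 76.6% |
| 0.9 | 0.500 | 3.16 | below 0.01% | 4.7% | 96.6% |

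The paired test holds its type I error between 4.9% and 5.1% throughout. The independent test's apparent power advantage at negative ρ comes only from its inflated type I error.

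For a difference as large as 4.7 the loss is small: 90%, 94% and 96% with the independent test at ρ = 0.5, 0.7 and 0.8, against 98%, 99.9% and 100% paired.

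**Check on a mixed model as the remedy.** A model with only a random intercept for eye imposes one common, non-negative correlation on all 11 locations. As an assumed example with equal SDs, let one location correlate −0.3 with a second and −0.2 with the other nine, and let the remaining 45 of the 55 pairs correlate +0.5. The average correlation is (−0.3 − 1.8 + 22.5)/55 = 0.371. A common-correlation analysis then uses a variance proportional to 1 − 0.371 = 0.629 for the first contrast, where the true value is 1 + 0.3 = 1.3. Its SE is too small by √(1.3/0.629) = 1.44, so the 1.96 cut-off acts like 1.96/1.44 = 1.36, a type I error of about 17%. That is worse than the 8.4% of the test it would replace.

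**The case against.** The strongest reply is that the error does little harm. The only comparison the study is powered for is between the two groups. The objective of developing variables for keratoconus detection also rests on that comparison, and there the independent-samples test suits the design. The primary objective is descriptive and has its own descriptive plan, the mirrored superimposition of left on right eyes. With positive correlation the test errs on the safe side, and for large regional differences it still has ample power. The magnitude also rests on assumed values: the protocol gives no ρ and no regional difference, its SD comes from an epithelial comparison between groups, and it gives no SD for stroma.

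Most of this stands, and it limits the point. A reader might infer more than the protocol supports in four ways:

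- **That the study's core analysis is invalid.** The within-group contrasts bear on the primary objective, but they are not the powered comparison.
- **That the between-group tests or the sample size fall.** They do not. With one eye per participant the groups are independent, and 35.5 reproduces.
- **That false positives are to be expected.** Thinning over the cone with thickening around it is a pattern of means. It gives negative correlation only if the two vary together from eye to eye, which nothing in the protocol shows. Nor could it hold everywhere: a correlation common to 11 locations cannot be below −1/10.
- **That every summary is wrong.** Means, SDs and standard errors at a single location are unaffected. Only the standard error of a difference between locations is wrong.

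What the reply does not remove is the mismatch itself. Under the stated assumptions the independent test's standard error is right only at ρ = 0, which is implausible for points on one cornea.

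**Conclusion.** The point holds for comparisons between locations within a group, and only there. The protocol assigns them a test whose independence assumption its own design rules out.

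The direction depends on ρ. In the plausible positive case the test is conservative: type I error is about 0.7%, 0.1% and 0.01% at ρ = 0.5, 0.7 and 0.8, and power for a 2-unit difference falls to between about one tenth and two fifths of that of the paired test (8.4/76.6 = 0.11; 16.2/39.5 = 0.41). Inflation above 5% needs negative correlation, which is an assumption.

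The SE ratios and type I errors do not depend on the value of σ, provided it is equal at the two locations. The power figures depend on the ratio 2/5.0 and say nothing specific about stroma. The mismatch itself needs none of these assumptions, and because it is explicit, touches the primary objective and is almost free to correct, it should be corrected before analysis.

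**What to change.** Split the sentence in the Statistical Analysis Plan section. Keep the independent-samples t test for group one against group two at corresponding locations. State that different locations within a group are compared with the paired t test, with the eye as the pairing unit. The cost is one sentence: the data, the participants and the sample size do not change.

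If a mixed model is preferred, it should have an unstructured or heterogeneous within-eye covariance across locations, not a simple random intercept. That takes more specification than one sentence, and the paired t test is sufficient.

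Pairing does not cure a separate problem with the thickest-epithelium locations along the steepest meridian. They are chosen by their own measured value, so contrasts with them are biased by selection under either test.
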